#### Primary Safety Analysis

Statistical analyses of the primary safety outcome will be conducted in the as‐treated population, including participants who have received a randomized procedure in whole or in part. Safety outcomes will be summarized descriptively and compared using χ^2^ or Fisher's exact tests, as appropriate. Interstage events in the hybrid arm will be captured and reported transparently as part of the overall safety assessment.

#### Secondary Analyses

Repeated‐measure continuous outcomes, including LVEF, LA volume, biomarkers, and quality‐of‐life scores, will be analyzed using linear mixed‐effects models with the time‐by‐treatment interaction fixed effect indicating the treatment effect. Binary secondary end points (eg, freedom from arrhythmia on antiarrhythmic medication, binary improvement in New York Heart Association class) will be analyzed using models analogous to those used for the primary analysis. Secondary and subgroup analyses are supportive and exploratory.

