### Patient Population

#### Inclusion Criteria

Age ≥18 yearsPersistent or long‐standing persistent AF (as defined by current guidelines)^1^
LVEF <50%*At least moderate LA dilatation (LA volume index ≥42 mL/m^2^)*Suitable for either procedure (clinical equipoise)

*As measured on transthoracic echocardiography in line with current guidelines.^35^ The LVEF threshold (<50%) is intended to capture both HF with mildly reduced ejection fraction (LVEF 40–49%) and HF with reduced ejection fraction (LVEF <40%). Baseline LVEF will be summarized both as a continuous variable and in prespecified clinically relevant categories (eg, <40% and 40%–49%).

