#### Secondary and Exploratory End Points

Secondary and exploratory end points will use data from investigations evaluated over the 12‐month follow‐up and are listed below:
Freedom from any atrial arrhythmia lasting >30 seconds after a single completed procedure on class I/III AADs.Freedom from atrial arrhythmias after any redo procedures (on or off class I or III AADs). This end point accounts for the overall success rate when additional ablations are performed.LV structural remodeling, as measured by change in LVEF in response to either procedure (from pre‐ to postablation echocardiography up to 12 months).LA remodeling in response to either technique (as measured from pre‐ to postablation echocardiography up to 12 months).Change in NT‐proBNP and prespecified circulating biomarkers (including CRP, lipid profile, renal function, and complete blood count) from baseline up to 12 months.To evaluate the effects of the interventions on symptoms, as assessed by change in the modified European Heart Rhythm Association score and New York Heart Association functional class from baseline up to 12 months after ablation.To evaluate the effects of the interventions on quality of life, as assessed by change (from baseline) in 3 highly validated quality‐of‐life scores:
European Quality 5 Dimensions 5‐Level scale^50^
AF Effect on Quality‐of‐Life Questionnaire^51^
Minnesota Living With Heart Failure Questionnaire^52^

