#### Statistical Threshold

All tests will be 2‐sided, with a *P* value <0.05 considered statistically significant. Estimates will be interpreted in the context of effect sizes and CIs. Analyses will be performed using R version ≥4.3 (R Foundation for Statistical Computing, Vienna, Austria), SAS version 9.4 (SAS Institute, Cary, NC), or equivalent validated analytical platforms. No formal interim efficacy analyses are planned.

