### Sample Size Estimation

The sample size was calculated on the basis of expected differences in arrhythmia‐free survival between the 2 treatment arms. Estimates will be interpreted in the context of CIs and effect size rather than significance alone. Prior data from a pilot study^55^ and published trials and analyses^5^, ^30^ were used to estimate procedural success rates, which were interpreted conservatively given the high‐risk nature of the study population. The sample size is based on a 1:1 randomized allocation to test the superiority of HA over CA. The power calculation assumed an anticipated incidence of sinus rhythm of 70% in the hybrid arm and 43% in the catheter arm. Using these numbers, with a standard α level of 0.05 and 80% power, 52 patients per arm (104 total) would be required to demonstrate the superiority of HA over CA. To account for potential dropout, loss to follow‐up, and estimation uncertainty, a 10% attrition rate and an additional 5% safety margin were applied. The final enrollment sample size was set at a minimum of 120 patients (60 per arm). The trial is powered for the primary efficacy end point; secondary and subgroup analyses are supportive and exploratory.

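### Change in NYHA class is the end point, but the only analysis named for it is improved versus not improved, without baseline class; this merges worsening with no change and discards information (minor, secondary outcome)

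*Protocol article*

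**What the plan says.** Under Secondary and Exploratory End Points, the protocol article sets the symptom end point as "change in the modified European Heart Rhythm Association score and New York Heart Association functional class from baseline up to 12 months after ablation". So the quantity of interest is movement on two ordered scales, in either direction.

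Under Secondary Analyses, NYHA appears once, in the sentence on binary secondary end points. "binary improvement in New York Heart Association class" is given as an example, and such end points "will be analyzed using models analogous to those used for the primary analysis". Primary Efficacy Analysis describes that model: Poisson regression with robust variance, adjusted for the two randomization factors, age category and sex. Baseline NYHA class is not in it. The outcomes listed for linear mixed models (LVEF, LA volume, biomarkers, quality-of-life scores) do not include NYHA, and no ordinal analysis is named. The article does not say how the modified EHRA score will be analysed.

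The inclusion and exclusion criteria require LVEF below 50% and an LA volume index of at least 42 mL/m², among other conditions, but set no minimum NYHA class.

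On status, Sample Size Estimation says: "The trial is powered for the primary efficacy end point; secondary and subgroup analyses are supportive and exploratory".

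**The concern.** The named analysis is coarser than the end point that it serves. Three things follow from the definition alone:

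- **Worsening equals no change.** A patient who moves from class II to IV and one who stays in class II are both not improved.
- **Class I entrants carry no information.** They cannot improve, so they count as non-improvers under either treatment. Benefit (staying in class I) and harm (leaving it) look the same.
- **Size of change is lost.** A two-class gain counts the same as a one-class gain.

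Leaving baseline class out of the model adds to this. A chance imbalance between arms in starting class is not corrected, and the precision that baseline would bring is not used. At stake is how well one symptom measure describes the two strategies, when Treatments acknowledges that the hybrid strategy carries more procedural burden up front.

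**Working it through.** **1. The plan's own figure.** The article gives one power calculation, for the primary end point: "an anticipated incidence of sinus rhythm of 70% in the hybrid arm and 43% in the catheter arm", two-sided α 0.05, 80% power. With p̄ = (0.70 + 0.43)/2 = 0.565:

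n per arm = [1.960·√(2·0.565·0.435) + 0.842·√(0.70·0.30 + 0.43·0.57)]² / (0.70 − 0.43)² = 51.7, so 52.

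This matches the stated 52 per arm (104 in total). The enrolment target also follows: 104 × 1.15 = 119.6, or 104 × 1.10 × 1.05 = 120.1, so 120. No figure of this kind is given for NYHA.

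**2. What the binary variable keeps.** Four classes at baseline and four at 12 months make 16 cells. Six are improvement, four no change and six worsening. The binary analysis sets the 6 improvement cells against the other 10. In the class I row, none of the four cells is an improvement.

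**3. Power under assumed inputs.** The documents supply only the sample size, α and 1:1 allocation. Everything else is assumed:

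- latent normal scale with cut-points at shares of 15/45/35/5% for classes I–IV
- baseline class I either excluded or allowed (15%)
- baseline-to-12-month correlation 0.3, 0.5 or 0.7
- improvement of 0.5 SD in the catheter arm, with an added treatment shift of 0.3, 0.5 or 0.7 SD
- 52 per arm, 2000 runs per scenario

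Three analyses were compared: a two-proportion test of improved or not; a Wilcoxon rank test on class change; and a linear model of 12-month class on treatment and baseline class, standing in for an adjusted ordinal model. Selected results (ratios from unrounded power):

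| Class I at entry | Correlation | Shift (SD) | Binary | Rank test | Adjusted | Binary/rank | Binary/adjusted |
|---|---|---|---|---|---|---|---|
| none | 0.3 | 0.3 | 20% | 21% | 29% | 0.94 | 0.67 |
| none | 0.5 | 0.5 | 54% | 60% | 73% | 0.90 | 0.73 |
| none | 0.7 | 0.7 | 93% | 96% | 98% | 0.96 | 0.94 |
| 15% | 0.3 | 0.5 | 36% | 43% | 65% | 0.84 | 0.55 |
| 15% | 0.5 | 0.5 | 42% | 49% | 70% | 0.85 | 0.59 |
| 15% | 0.7 | 0.7 | 82% | 89% | 98% | 0.93 | 0.84 |

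Over all 18 scenarios:

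- Binary against rank test: power ratio 0.84–0.96, effective sample size 0.75–0.87.
- Binary against adjusted, no class I: power ratio 0.67–0.94, effective sample size 0.54–0.68.
- Binary against adjusted, 15% class I: power ratio 0.55–0.84, effective sample size 0.39–0.56.

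**4. Where the gap comes from.** At correlation 0.5, shift 0.5 SD and 15% class I, the gap to the adjusted analysis is 70 − 42 = 28 points. Keeping the ordering of change accounts for 49 − 42 = 7 of these; the other 21 come from modelling 12-month class with baseline as a covariate. With no class I the split is 6 of 19.

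**5. How far the range can move.** A further run with 25% in class I, a 0.5 SD shift and correlations of 0.4 and 0.6 gave 0.304/0.654 = 0.46 and 0.375/0.700 = 0.54 for binary against adjusted. The lower bound therefore depends on how many class I patients enrol, which the documents do not say.

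**The case against.** Several objections carry weight.

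- **Status.** Secondary analyses are declared supportive, and the trial is not powered for them. This stands and fixes the importance as minor. A reader might take NYHA for a key outcome. The documents do not call it one: in the Discussion that word goes to the quality-of-life measures, and NYHA is not named there.
- **It is only an example.** The binary form is introduced as an instance of binary end points, and a statistical analysis plan not shown here could add an ordinal analysis. That cannot be ruled out. But the article places NYHA among the binary outcomes and names no other analysis of it, although its own end point is change.
- **Deterioration is seen elsewhere.** New or worsening heart failure is a MACE component, counted within 30 days of any procedure or part of one. Adverse events run to 12 months and interstage events are captured. LVEF, NT-proBNP and the Minnesota questionnaire are modelled as continuous measures. This largely stands: a reader might infer that the trial is blind to worsening, and the documents do not support that. Only the NYHA analysis is.
- **Class I patients dilute but do not bias.** Correct, since randomization balances them in expectation. The loss is of information.
- **Preference.** A responder proportion with a risk ratio is easy to read, and proportional odds is itself an assumption. That is a reason to keep percent improved on display, not to make it the only named analysis.

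**Conclusion.** The point holds as a minor mismatch between a secondary end point and its named analysis. The merging of worsening with no change, and the silence of the binary variable on class I entrants, follow from the definition and need no assumed number.

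The size of the power loss does need assumptions. With 0% or 15% of patients in class I, the binary analysis kept roughly 55–95% of the power of a baseline-adjusted analysis of 12-month class, and 84–96% of that of a rank test on change.

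A reader might conclude that dichotomising roughly halves power. The documents do not support this as a general statement: they give no NYHA distribution, the figure is approached only with enough class I patients or weak baseline correlation, and it charges to dichotomising what is partly a gain from baseline adjustment. Sensitivity to inputs is plain. With the same 15/45/35/5% mix, 54 per arm and a log odds ratio of 0.9, one simulation gave 32% against 65% for an adjusted proportional-odds model. Another, with different assumed baseline dependence, drift and cut-points, gave 40–44% against 58–64%.

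The primary analysis and the sample size are unaffected.

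**What to change.** In Secondary Analyses, take NYHA out of the binary examples and state that:

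- 12-month NYHA class will be analysed with a proportional-odds model adjusted for baseline class, age category and sex, merging sparse classes if needed (at an assumed 5% share, class IV would hold about 0.05 × 104 = 5 patients at baseline);
- the baseline-to-12-month shift table will be shown by arm;
- percent improved will be reported as a descriptive summary;
- the modified EHRA score will be handled by the same ordinal approach. The article does not say that score will be dichotomised, so this fills in a method rather than correcting one.

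The cost is analysis wording only. Table 1 already schedules symptom scoring at baseline and at every follow-up visit, so no new data are needed. The downsides are that an odds ratio is less familiar than a percentage improved, and that the proportional-odds assumption has to be checked.

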#### Missing Data

The primary analysis will use all available rhythm data collected according to the prespecified visit schedule, with the 12‐month assessment defined as T_0_+365±30 days. For the binary primary end point, participants will be classified as having recurrence if atrial arrhythmia is documented at any time after the blanking period and within the follow‐up period. Participants with insufficient rhythm data to determine 12‐month recurrence status will be identified, and the extent of missing primary end point data will be reported by treatment arm. Prespecified sensitivity analyses will assess the robustness of the findings under conservative assumptions, including classifying participants with missing end point status as having experienced a recurrence. These analyses are intended to assess the potential impact of missing data on the primary strategy‐level comparison. The frequency and reasons for nonexposure, withdrawal, and loss to follow‐up will be summarized descriptively by treatment arm to assess potential differential attrition.

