### Statistical Analyses

The primary efficacy outcome will be analyzed using a modified intention‐to‐treat approach, including all randomized patients who undergo any component of their allocated ablation strategy. This approach was prespecified to reflect the pragmatic strategy‐based design of HALT AF, recognizing that the trial evaluates procedural strategy effectiveness and that patients without procedural exposure do not enter the risk set for procedural efficacy. Patients randomized but not exposed to any procedural component will be described separately and excluded from efficacy analyses. Participants who undergo partial delivery of the allocated strategy but are unable to complete the intended lesion set for any reason will remain in the primary efficacy analysis and will be handled in accordance with the prespecified end point rules. As a conservative sensitivity analysis, patients who are randomized but not exposed to any procedural component will be classified as treatment failures for the 12‐month binary end point.

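### Scoring missing end points as recurrence in both arms is conservative for each arm's success rate, but not necessarily for the hybrid-versus-catheter contrast it is meant to test

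*Protocol article*

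**What the plan says.** Under Missing Data, the primary analysis uses the available rhythm data, and participants whose 12-month status cannot be determined are identified and counted by arm. Robustness is then examined under assumptions described as conservative, "including classifying participants with missing end point status as having experienced a recurrence". The section states that the purpose is to gauge the effect of missing data on the strategy-level comparison. Reasons for non-exposure, withdrawal and loss are to be summarised by arm, with differential attrition in mind.

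A parallel rule stands at the opening of Statistical Analyses. Patients who never receive any part of their allocated procedure are left out of the primary efficacy analysis, and then: "As a conservative sensitivity analysis, patients who are randomized but not exposed to any procedural component will be classified as treatment failures".

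Neither rule is limited to one arm. The comparison they serve is directional: "The sample size is based on a 1:1 randomized allocation to test the superiority of HA over CA". The Primary Efficacy Analysis section reports it as a risk ratio and a risk difference.

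**The concern.** A sensitivity analysis is conservative for a superiority claim if it can be relied on to move the estimate towards no difference. Scoring every missing outcome as a failure in both arms does not do that. It lowers both success rates, and the arm with more missing outcomes is lowered more. When that arm is the comparator, the apparent benefit of the experimental arm can grow.

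Allocation is open-label, so unequal withdrawal is possible, and the plan itself looks for it. If it occurred on the catheter side, a check reported as conservative could show a stronger result than the primary analysis. A reader would take that as reassurance although no assumption unfavourable to hybrid had been tested.

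**Working it through.** **Inputs from the protocol article**
- Success rates (Sample Size Estimation): "The power calculation assumed an anticipated incidence of sinus rhythm of 70% in the hybrid arm and 43% in the catheter arm".
- Size: "with a standard α level of 0.05 and 80% power, 52 patients per arm (104 total) would be required"; enrolment of 120, 60 per arm.
- Allowance: "a 10% attrition rate and an additional 5% safety margin were applied", with no split by arm.
- Tests (Statistical Threshold): "All tests will be 2‐sided".

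**Plan's own figure.** The two-proportion formula with pooled variance under the null, two-sided 0.05 and 80% power, for 70% versus 43%, gives 51.7, so 52 per arm. Then 104 × 1.15 = 119.6, so 120. The sample size reproduces and is not in question.

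**Effect of the rule on the contrast.** Let p be the true success rate and m the missing fraction in an arm (H hybrid, C catheter), with missingness unrelated to outcome within an arm (an assumption). Scoring missing as failure gives an expected rate of p(1−m).
- Risk ratio: (p_H/p_C) × (1−m_H)/(1−m_C). It exceeds the true value whenever m_C > m_H.
- Risk difference: (p_H − p_C) − (p_H·m_H − p_C·m_C). It exceeds the true value only if m_C/m_H > p_H/p_C. At the design rates the threshold is 0.70/0.43 = 1.63. With no true effect it is 1, so any catheter excess inflates it.

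**At the design rates (true difference 27.0 points, true ratio 1.63)**

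| Missing, hybrid / catheter (assumed) | Rates after rule | Difference (points) | Ratio |
|---|---|---|---|
| 10% / 10% | 63.0% vs 38.7% | 24.3 | 1.63 |
| 4/60 / 6/60 | 65.3% vs 38.7% | 26.6 | 1.69 |
| 5% / 15% | 66.5% vs 36.6% | 29.9 | 1.82 |
| 0% / 20% | 70.0% vs 34.4% | 35.6 | 2.03 |
| 15% / 5% | 59.5% vs 40.9% | 18.6 | 1.46 |

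The second row matters: catheter loses more, yet the difference is slightly below its true value while the ratio is above it. The last row shows the rule working against hybrid.

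**With no true effect.** In a simulation (200,000 runs, 60 per arm, 56.5% success in both arms), two-sided rejection under the rule is about 5% at 10%/10% missing. It is about 10% at 5%/15%, nearly all favouring hybrid, and about 25% at 0%/20%.

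**Illustrative counts.** Assume 2 hybrid and 8 catheter outcomes missing. That is 10/120 = 8.3%, inside the 10% allowance. Pearson chi-square without continuity correction:
- Available data: 36/58 (62.1%) vs 24/52 (46.2%), +15.9 points, p=0.094.
- Plan's rule: 36/60 vs 24/60, +20.0 points, p=0.028.
- Tilted against hybrid (missing hybrid = failure, missing catheter = success): 36/60 vs 32/60, +6.7 points, p=0.46.

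At rates close to the design, with 3 hybrid and 9 catheter missing, 40/57 vs 22/51 gives p=0.0046. The rule gives 40/60 vs 22/60, p=0.0010. The tilted case gives 40/60 vs 31/60, p=0.095.

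**Opposite imbalance.** With 9 hybrid and 3 catheter missing, 36/51 vs 25/57 (+26.7 points, p=0.005) becomes 36/60 vs 25/60 (+18.3 points, p=0.045). Here the rule is conservative.

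**The case against.** Several points on the other side stand.

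- **Direction is unknown.** The burdens the article describes fall on hybrid: two admissions, two general anaesthetics, surgery, and a longer path to the 12-month visit. Greater hybrid loss is at least as plausible, and the rule would then be conservative. Patients who miss stage 2 stay in the analysis and are classified from available data, so non-completion alone does not make them missing.
- **Not every catheter excess inflates the risk difference.** Below a ratio of about 1.63 at the design rates, it does not.
- **Truth may match the rule.** If the missing catheter patients did recur, scoring them as failures adds no bias.
- **Never-treated patients are a different case.** They have persistent AF and received no trial ablation. Failure is their most credible status, and scoring untreated catheter patients as successes would not be credible. That check also restores all randomised patients. Only its label is open to question.
- **Other analyses give some protection.** The time-to-event analysis censors participants without recurrence rather than failing them, and missingness is reported by arm, so an imbalance would be visible. Neither shows whether the binary conclusion survives it.

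A reader might infer that the plan lacks a tipping-point analysis. The documents do not support that: the list of sensitivity analyses is open-ended, and the SAP is not shown. A reader might also infer that the rule could turn a negative trial positive. It cannot, because it is a sensitivity analysis and the primary result stands. Nor is +15.9 points with p=0.094 evidence of no effect.

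**Conclusion.** The point holds as one about a stated property of a named check. The Missing Data section presents the same-value rule as conservative for the between-arm comparison, and whether it is depends on attrition by arm that is not yet known. It favours hybrid on the risk ratio whenever catheter has the larger missing share. It favours hybrid on the risk difference when the catheter-to-hybrid missingness ratio exceeds the ratio of success rates (about 1.63 at 70% versus 43%, or 1 with no true effect). It works against hybrid in the opposite case.

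The size cannot be fixed from the documents. The shift from p=0.094 to p=0.028, against p=0.46 in the tilted case, rests on an assumed 2-versus-8 split and assumed observed rates; it shows what is possible, not what is expected. The formula results assume missingness unrelated to outcome within each arm. The primary estimate and the sample size are unaffected. What is at risk is how far the robustness check can be trusted.

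**What to change.** - **Missing Data:** do not describe the same-value rule as conservative for the treatment difference. Add an arm-specific tipping-point analysis for missing end points, varying the number of successes assigned among the missing in each arm. Include the case tilted against hybrid, keep the present rule as one cell, and report where the conclusion changes. In the 2-versus-8 illustration with missing hybrid patients as failures, one catheter success gives 36/60 vs 25/60 (p=0.045) and two give 36/60 vs 26/60 (p=0.068), so the tipping point is two of eight. If the SAP already contains such an analysis, a reference to it is enough.
- **Statistical Analyses:** keep scoring never-treated patients as failures, presented as a plausible check on all randomised patients, but do not call it conservative for the between-arm difference.

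The cost is a few lines of code and wording, with no extra patients or data. The downside is that the tilted case is severe, and a positive result may look less robust.
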